### Adverse events record, withdrawal, and safety measures

Participants will be regularly monitored for any adverse events during the intervention by the assigned physician by reporting on the mobile application. The communication between the participant and the physician is daily to monitor and adjust the drug dosage until the blood sugar levels have stabilised. Any adverse events that occur during the intervention will be documented along with the methods employed to address them. Any adverse effects that may lead to a participant’s discontinuation or occur during the course of the study will be followed up until a satisfactory solution is reached. This information will also be included in the final report.

Participants will have the right to withdraw from the trial at any time without providing any explanation. The study will discontinue the subject’s participation if any of the following conditions occur: a) the subject fails to comply with the study protocol and requirements; b) there is a significant deviation from the study protocol; c) the subject becomes pregnant during the study; d) the subject develops a new illness that warrants exclusion based on the criteria mentioned above; e) continuation in the study is deemed harmful to the subject’s health, f) the subject is lost to follow-up, and g) the trial is cancelled.

Any deviation from this protocol will be reported to the Ethics Committee, and approval will be sought.

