### Intervention

The Freedom from Diabetes protocol is a comprehensive one-year ILI focused on four key components: dietary modifications, physical activity, psychological support, and medical management. Each participant is supported by a dedicated team of experts, which includes a physician, a dietitian, a physical therapist/certified yoga professional, a psychologist, a mentor (who is a past participant volunteering to guide the new participant), and a monitor (for follow-ups and reminders for lab tests and appointments). Participants also have access to a mobile application that facilitates communication with the team via voice/video calls and text messages.

The interventions implemented in the DIRemI study are shown in Fig 2. The four protocols are divided into several phases, each designed to introduce incremental modifications, initially focusing on diet and exercise. Subsequently, both are enhanced by the addition of emotional stress release and goal setting. The ultimate objective of the phases is to render the participants self-sufficient and able to sustain the changes. Progression to the subsequent phase is contingent on achieving the predetermined target for the previous phase. The goals for each phase of the program are established collaboratively with the patient’s healthcare team, which comprises a dedicated physician, dietitian, and physical therapist. Throughout the program, these objectives serve as a guide for patient progress and are periodically reviewed and adjusted as necessary.

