#### Mode of delivery

The intervention is delivered online through video meetings and conferences. Throughout the year, the team of experts keep in touch with the participants through an average of 63 calls per year. In addition to the 12 monthly sessions, group sessions covering the primary focus for that month, additional group activities such as mid-month catch-up sessions, and diet/exercise-wiser sessions are conducted to check and improve adherence and motivation. Participants have access to a dedicated mobile application to communicate with their team and regularly track and update their vitals (fasting and postprandial blood sugar levels, weight, and blood pressure) along with their diet and exercise regimen. Participants are also provided with region-specific plant-based recipes to avoid drastic changes in their existing diet.

For exercise recommendations, fitness level, age, physical limitations, and preferences are considered. Phases 1 and 2 have pre-recorded exercise sessions which are relayed in the morning and evening for six months, catering to differing needs. Additionally, other exercise videos for different physical limitations like spondylosis, frozen shoulder, and knee issues that are provided based on the requirement and recommendation. The participants are guided individually by their assigned physical therapist.

Overall, diet, physical activity, and stress management are tailored to each participant’s individual needs, considering their comorbidities, age, sex, and fitness levels. In total, there are 600+ exercise videos, session videos, meditation audios, PDFs, and 400+ recipes to choose from, giving the participants variety and progression.

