### Control group (Routine medical care)

The control group will receive routine medical care along with education for management of T2D and its associated comorbidities based on current clinical guidelines.

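### The only stated adverse-event detection route belongs to the intervention programme, so the reported safety data cannot be validly compared between groups as written

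*Protocol article*

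**What the plan says.** Under Adverse events record, withdrawal, and safety measures, the protocol article gives the detection route: "Participants will be regularly monitored for any adverse events during the intervention by the assigned physician by reporting on the mobile application". The contact behind it is frequent: "The communication between the participant and the physician is daily to monitor and adjust the drug dosage until the blood sugar levels have stabilised". Recording is tied to the same period: "Any adverse events that occur during the intervention will be documented along with the methods employed to address them". A later sentence says that adverse effects that may end a person's participation or "occur during the course of the study will be followed up until a satisfactory solution is reached", and the section then adds: "This information will also be included in the final report".

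The application is introduced under Intervention: "Participants also have access to a mobile application that facilitates communication with the team". It appears again under Dietary modifications, Medical management, Mode of delivery and Adherence check, each time as part of the programme. The assigned physician is a member of the programme team (Intervention, Medical management). Mode of delivery adds contact by the team of experts at "an average of 63 calls per year".

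For controls, the article says: "The control group will receive routine medical care along with education for management of T2D". It describes no application, daily contact or adverse-event reporting route for them. Data collection in both groups is at baseline and at 6, 12 and 18 months (Sampling and recruitment process).

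**The concern.** A two-group trial that reports adverse events invites readers to set the counts side by side, whether or not a test is planned. That is only meaningful if an event of a given kind has a similar chance of being recorded in each group. Here one group has a physician in daily contact until glucose is stable and an application for reporting. For the other group, no means of finding events is stated.

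The question matters for this programme. It includes juice-fasting days of 300–500 kcal with drug-dose adjustment (Dietary modifications) in people who may be taking insulin or oral agents (Table 1). Whether events such as hypoglycaemia or hospital admission are more or less frequent than under routine care is something readers will want to know. With unequal capture, an excess in the intervention group could be real or could come from closer surveillance, and similar counts could hide a true difference.

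**Working it through.** The article gives no adverse-event rate, safety sample size or safety power, so there is no figure to reproduce. The main check is a comparison of the text.

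| Element | Intervention group | Control group |
|---|---|---|
| Who detects events | Assigned physician | Not stated |
| Channel | Mobile application | Not stated |
| Contact described | Daily until glucose is stable; team calls averaging 63 a year, not described as adverse-event contacts | Routine clinic care and education |
| Period covered by the stated route | During the one-year intervention | No counterpart defined |
| Months 12 to 18 | No route stated | No route stated |
| Adverse-event item in the data collection text common to both groups | None named | None named |

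The sentence on effects arising during the study is neutral as to group. It covers follow-up of events once they are known and does not say how an event in a control participant would become known.

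**Illustration of size.** Only the 180 per group comes from the article (Sample size determination). The risks and capture rates are assumptions. Let *p* be the true risk of at least one event, equal in both groups, and let *s*_I and *s*_C be the chances that the event is recorded.

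- Recorded risks are *p*·*s*_I and *p*·*s*_C.
- The apparent risk ratio is *s*_I / *s*_C, which does not depend on *p*.
- With *s*_I = 0.90: 0.90/0.70 = 1.29; 0.90/0.50 = 1.80; 0.90/0.30 = 3.00.

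The chance of a nominally significant excess in the intervention group, although true risks are equal, uses the normal approximation for two proportions at two-sided 5%:

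Φ{[(p₁ − p₂) − 1.96·√(2·p̄(1 − p̄)/n)] / √([p₁(1 − p₁) + p₂(1 − p₂)]/n)}, where p₁ and p₂ are the recorded risks, p̄ is their mean and n = 180.

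Worked case, p = 10% and control capture 50%: p₁ = 0.09, p₂ = 0.05, p̄ = 0.07. The null standard error is 0.0269 and the alternative standard error is 0.0268. Then (0.04 − 1.96 × 0.0269)/0.0268 = −0.47, and Φ(−0.47) ≈ 32%.

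| Control capture | Apparent risk ratio | True risk 10% | True risk 20% |
|---|---|---|---|
| 90% (equal) | 1.00 | 2.5% | 2.5% |
| 70% | 1.29 | 10% | 18% |
| 50% | 1.80 | 32% | 59% |
| 30% | 3.00 | 67% | 94% |

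The 2.5% is the upper tail of a two-sided 5% test. The distortion also works the other way: with 90% and 50% capture, a true risk ratio of 0.50/0.90 = 0.56 in favour of the programme would be recorded as 1.00.

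**The case against.** The strongest case is that the article leaves the control procedure unstated and does not fix it wrongly.

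- **No safety comparison is planned.** Safety is not among the objectives, the outcome measures or the named analyses. The article promises only that events are documented, followed up and reported. This stands. The harm falls on how the reported data can be read, not on a stated test.
- **Control events may well be recorded.** A reader might infer that the plan leaves control events unrecorded. The article does not say so. The follow-up sentence and the discontinuation rules apply to any participant, and controls attend clinics for routine care. This stands as a limit on the claim, but none of these passages supplies a detection method.
- **The detail may lie elsewhere.** The article condenses a fuller document, and Fig 1, the schedule for both groups, is not shown. Adverse-event collection in both groups could appear there. That cannot be excluded. But the text is not silent on detection: it states one route, and followed as written that route observes one group for one year.
- **The size is unknown.** A reader might want one headline ratio. Any such figure only restates the capture rates chosen; 80% and 20%, for example, give 0.80/0.20 = 4 by construction. The article gives no basis for any pair, so only a labelled range is defensible.
- **Equal capture would not settle the comparison.** The trial is open-label and non-randomised, and its groups come from different clinics. This is correct, and it limits what the fix can deliver.

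**Conclusion.** The point holds in a limited form. The one stated detection route depends on an application and a physician described only for the programme, and it covers only the intervention year. None is described for controls, or for months 12 to 18 in either group. As written, the adverse-event data promised for the final report cannot support a valid between-group comparison.

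The size cannot be determined from the article. Under assumed capture of 90% against 70%, 50% or 30%, equal true risks would appear as ratios of 1.29, 1.80 or 3.00. The accompanying false-excess probabilities further assume 180 analysed per group and a true risk of 10% or 20%. The co-primary outcomes, weight loss and remission, do not depend on this rule. The change should be made, but it does not threaten the main result.

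**What to change.** Add one structured adverse-event form, completed for every participant in both groups at the existing 6-, 12- and 18-month collections, with the same questions, definitions and recall period. It could ask about hypoglycaemia, hyperglycaemia needing care, hospital or emergency visits, and other events leading to treatment. State that any between-group safety statement rests on this form only. List application-reported events separately as intervention-group surveillance. The programme's own monitoring continues unchanged.

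The cost is about a page added to visits and standardised questionnaires that already exist at all three centres. Recall over six months is imperfect and may be somewhat better in the intervention group, whose members monitor themselves and log readings. Differential capture is therefore reduced, not removed, and the comparison remains non-randomised; the report should say both.

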#### Adherence check

Participants in the program are regularly encouraged to follow the protocol, and their adherence is assessed through monthly checks using a mobile application. These checks involve short multiple-choice questionnaires designed to evaluate participants’ adherence to the relevant interventions for that period. The monthly adherence scores are calculated and used to provide feedback to experts, who can then take appropriate action. At the end of the 12-month intervention period, monthly scores are combined to generate an overall adherence score for each participant. The purpose of these measures is to ensure that participants adhere to the program’s protocol and provide feedback to experts for any necessary actions.

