### Statistical analyses

Primary outcome measures will be analysed using two-sided statistical tests with a type I error rate of α = 0.05. Primary analysis will be performed using the intention-to-treat method. Categorical data will be compared between the two groups using chi-square or Fisher’s exact tests. Continuous data will be evaluated using parametric or non-parametric tests based on data distribution.

For outliers (± 3 standard deviation), efforts will be made to cross-check and obtain the correct values. Failing this, the case will be considered as missing data. In the case of random missing values, two separate analyses will be performed: one including the cases with missing data by choosing pairwise deletion and the other excluding it using listwise or case-wise deletion. A complete case analysis will be considered if differences are observed between the two analyses. In the case of non-random missing values, the imputation method may be used by replacing the missing value with the mean for that variable.

Potential adjustments for baseline values, age, gender, and disease duration may be considered. Multivariable linear and logistic regression analyses will be used to determine predictors of remission. Finally, subgroup analyses may be performed based on factors such as gender, age, comorbidity, diagnosis length, and severity to investigate potential variations in treatment responses.

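### Ending study participation for non-compliance, with later follow-up promised only for adverse effects, means the stated intention-to-treat primary analysis cannot be carried out as named

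*Protocol article*

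**What the plan says.** All references are to the protocol article.

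- **Adverse events record, withdrawal, and safety measures.** The list of grounds opens with "The study will discontinue the subject’s participation if any of the following conditions occur". Ground (a) is that "the subject fails to comply with the study protocol and requirements" and ground (b) that "there is a significant deviation from the study protocol". The same list contains loss to follow-up and cancellation of the trial. The only follow-up described beyond this point concerns adverse effects, which "will be followed up until a satisfactory solution is reached". Nothing is said about later weight, HbA1c or medication status.
- **Statistical analyses.** "Primary analysis will be performed using the intention-to-treat method". For values missing at random, two analyses are planned: "one including the cases with missing data by choosing pairwise deletion and the other excluding it using listwise or case-wise deletion". Then: "A complete case analysis will be considered if differences are observed between the two analyses". For values not missing at random, the mean of the variable may be substituted.
- **Adherence check.** For programme participants, "their adherence is assessed through monthly checks using a mobile application". The scores go to the experts, who may act on them.
- **Control group (Routine medical care).** Controls receive routine care and education. No adherence check is described.

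**The concern.** An intention-to-treat analysis keeps people who do not comply in the group they entered. Here, non-compliance is a reason to leave the study, and no outcome collection is described afterwards. The missing-data rules then either remove these people or give them an average value. The analysis named as intention-to-treat would in practice be close to an analysis of those who complied.

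Both primary outcomes, weight loss of at least 10% and remission, are exposed. People who abandon a strict diet and exercise plan are less likely to reach either. If such people are lost mainly from the intervention group, its success rates are overstated. No later analysis plan can recover measurements that were never requested.

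**Working it through.** The plan gives no non-compliance rate and no expected remission rate, so it has no figure of its own to reproduce on this point. The check is a reading of the sections together, followed by arithmetic on labelled assumptions.

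**Step 1. Does the rule end the study or only the programme?** The wording attaches to the study. The sentence before the list concerns withdrawal from the trial, ground (e) speaks of continuing in the study, and grounds (f) and (g) are study-level events. The study-level reading is the natural one.

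**Step 2. What happens to the outcomes of those discontinued?** Two arrangements would reconcile discontinuation with intention-to-treat: collecting outcomes anyway, or stating how discontinued people count in the binary outcomes. The article states neither. Listwise or complete-case analysis drops them. Pairwise deletion also leaves them out of any comparison that uses the missing outcome. Mean replacement, the option for non-random missingness, gives a non-complier the average result, largely that of people who stayed.

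**Step 3. Which group is more exposed?** The intervention includes juice-fasting days of 300-500 kcal, exercise six days a week, 56 days of group therapy and monthly adherence scores. Controls have routine care and education. Non-compliance is therefore both likelier and easier to see in the intervention group. This is an inference; the rule is worded for both groups.

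**Step 4. Size in the intervention group.** Let f be the fraction removed, r the remission rate among those retained and q the rate among those removed.

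Rate in all enrolled = (1 − f) × r + f × q, so overstatement = r − rate in all enrolled = f × (r − q).

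Assumed: f = 10-30%, r = 30-50%, q = 0.

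| f | r | q | Rate in all enrolled | Overstatement |
|---|---|---|---|---|
| 10% | 30% | 0 | 27% | 3 points |
| 20% | 40% | 0 | 32% | 8 points |
| 30% | 40% | 0 | 28% | 12 points |
| 30% | 50% | 0 | 35% | 15 points |
| 20% | 40% | 10% | 34% | 6 points |

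The last row shows the bias shrinking when some of those removed would remit.

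**Step 5. Effect on the test.** Suppose there is no true effect, 180 are enrolled per group (Sample size determination), and only failures in the intervention group are removed. The observed intervention rate is p / (1 − f). With p = 10% and f = 30%, 126 remain and the rates are 0.10 / 0.70 = 14.3% against 10.0%. By the normal approximation for two proportions at two-sided 0.05, the pooled standard error is 0.0374 and the unpooled 0.0384. The chance of a significant result favouring the intervention is Φ((0.0429 − 1.96 × 0.0374) / 0.0384) = Φ(−0.79), about 21% against a nominal 2.5%. With f = 10% it is about 5%, and with f = 20% about 11%. If 30% of each group, all failures, were removed, both rates would be 14.3% and no spurious difference would arise.

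**The case against.** The strongest reply is that ending participation is not exclusion from the analysis. The article never says that discontinued people are left out or that their outcomes go uncollected, and a condensed article may leave post-discontinuation follow-up to the full protocol. This stands in part: discontinuation alone does not contradict intention-to-treat, and a reader who infers an outright contradiction goes too far. But the article is not merely silent. It ends study participation, limits its promise of later follow-up to adverse effects, and states deletion and mean replacement as the handling of gaps. Those provisions together do not deliver the analysis named.

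A second reply is that the adherence scores have another purpose. They feed back to experts, carry no removal threshold and are combined into a 12-month score for each participant, which suggests that poor adherers are expected to stay. Failing to comply could also mean not sending weights or laboratory reports, which applies to controls too. This stands as a limit. A reader might infer that the intervention group is filtered and the control group is not; the documents support that only as a probable imbalance.

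A reader might also infer that the 30% allowance in Sample size determination results from this rule. Nothing supports that: it is given as an allowance for dropout and loss to follow-up, and removal under the rule could at most contribute to it.

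Finally, the size rests on assumed rates. That is correct, and the result is given only as a range.

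**Conclusion.** The point holds in a limited form. As written, the withdrawal rule and the missing-data rules together prevent the named intention-to-treat analysis from being carried out, because non-compliers' 12-month outcomes would not be collected and would then be dropped or averaged.

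The bias probably favours the intervention, since that group has more to fail at and is scored monthly. The documents do not fix its size. The range of 3 to 15 points applies to the intervention group's remission rate and rests on the three assumptions in the working (10-30% removed, none remitting, 30-50% remission among those retained). It is smaller if some of those removed would remit. The bias in the between-group difference is also smaller if controls who have not remitted are removed too.

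**What to change.** 1. Reword the withdrawal section so that non-compliance or a significant deviation may end participation in the programme but not outcome follow-up. The safety grounds for stopping the intervention are not affected by this change.
2. Ask everyone who has not withdrawn consent for weight, HbA1c and medication status at 6, 12 and 18 months, and analyse them in the group they entered.
3. In Statistical analyses, replace deletion and mean replacement with a method that keeps all enrolled participants, such as multiple imputation.
4. Report alongside it, as a sensitivity analysis, the result with unknown status counted as failure. This should not be the only or primary rule, because it can favour the better-retained group. With true remission of 20% in both groups and random loss of 10% against 30%, it gives 0.20 × 0.90 = 18% against 0.20 × 0.70 = 14%. The programme's average of 63 calls a year could plausibly produce better retention in that arm.

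The cost is protocol wording, continued requests for home weights and laboratory reports that are already planned, and possibly a lower reported success rate.
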